### Statistical analysis

2.12.

All data will be analyzed according to the intention-to-treat principle (16, 17). The baseline data will be compared and analyzed using descriptive statistics [mean (SD), proportion, or median (range)] to determine whether balanced groups were obtained after randomization. Student's *t*-test or Mann–Whitney's *U* test will be used to compare continuous variables. Categorical variables will be compared using *χ*^2^ or Fisher's exact tests. All comparative analyses will be reported with point estimates [means (SD) or odd ratios (ORs)], 95% CIs, and *p*-values. Statistical significance will be set at *p *< 0.05. Non-inferiority margins will be set as listed in Table 2. Statistical analysis will be performed using appropriate statistical software (e.g., SPSS version 22.0 or Stata).

**Table 2 T2:** Non-inferiority margins.

Outcome measurements	Expected differences	Non-inferiority margin
JOA	<5	5
VAS	<5	5
muscle strength test	<5	5
Sphincter function test	<5	5

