## Introduction

1.

Although spinal intradural extramedullary (IDEM) tumors grow slowly, the spinal canal is limited by its small volume, and the spinal cord and nerve roots are compressed or invaded by the tumor, which causes sensory, motor, and autonomic dysfunction (1). The treatment of spinal IDEM tumors focuses on removing tumor tissue and decompressing the nerve root and spinal cord to improve nerve function (2, 3). Traditional surgical methods include laminectomy (total laminectomy and hemilaminectomy), laminotomy, and laminoplasty (LP) (4). Among the available spinal surgeries with different indications, a “standard surgical procedure” for treating spinal IDEM tumors has not been determined. Owing to the development of minimally invasive spine surgery (MISS), the paraspinal mini-tubular technique (PMTT) has been introduced for treating IDEM tumors (5–7). Most studies reported that tubular spine surgeries reduced the volume of estimated blood loss (EBL) and shortened the length of hospital stay. The postoperative outcome of the patients was good, with fewer complications. These together promoted the development of MISS. A microscope-assisted PMTT has a larger operating space than endoscopy and a relatively wide range of indications, including various types of intervertebral disc herniation, spinal stenosis, spinal tumors, and spinal cord injuries (8). With the popularization and application of PMTT, the safety and effectiveness of treating spinal-related diseases have been increasingly recognized. Compared with traditional surgery, the microscope-assisted microtubular technique has the advantages of less tissue damage, fewer complications, shorter length of hospital stay, reduced postoperative pain, improved surgical efficiency, and reduced risk of spinal instability (9–11). To the best of our knowledge, prospective, randomized controlled trial studies with a large sample comparing the safety and effectiveness of the PMTT and LP in the treatment of spinal IDEM tumors, have not been conducted. Therefore, this study aims to explore the difference in the therapeutic effect of the PMTT and LP in the treatment of patients with spinal IDEM tumors through a prospective, multi-centered, non-inferiority randomized clinical trial. The main hypothesis is that PMTT has advantages in cost-effectiveness, and it is equivalent in safety and efficacy to LP.

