### Study description

2.1.

The FJMUUH05 trial is designed as a prospective, multi-center, non-inferiority RCT with two parallel groups in eight hospitals from seven provinces in China. A total of 280 patients aged 10–75 years with confirmed radiographic diagnosis and IDEM tumor lengths of less than three segments will be enrolled in this study. After the patients sign a written informed consent to participate, they will be randomized to one of the two groups: the PMTT group, which will receive paravertebral approach and microtubular technique treatment, and the LP group, which will receive laminoplasty treatment. The follow-up period will last for two years. The study is registered at https://www.chictr.org.cn, which can be accessed online (ChiCTR2100047582). Consent (version date January 21, 2021, V.1.0) will be obtained by an investigator who will comply with applicable regulatory requirements and adhere to the ethical principles of the Declaration of Helsinki. The time points, randomization, treatment allocation, and assessment are summarized in Figure 1.

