### Outcome measurements

2.8.

Patients must have an indication for the surgery. The primary outcome variable is the JOA score. The secondary outcome variables include the VAS score, physical examination findings, length of hospital stay, expenses, and complications. Outcomes will be measured on the first postoperative day, and thereafter at the 1st week, and at 1, 3, 6, 12, and 24 months after surgical treatment. A physical examination will be conducted after 1 week, 1 month, and 12 months from the day of the surgery (Table 1). The non-inferiority margin for the primary outcome is five.

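### Section 2.12 gives a non-inferiority trial only difference tests at p<0.05, and no rule links its confidence intervals to its margins

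*Protocol article*

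**What the plan says.** All references are to the protocol article.

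- **Design.** Section 2.1: "The FJMUUH05 trial is designed as a prospective, multi-center, non-inferiority RCT with two parallel groups". Sections 1 and 2.13 also call the trial non-inferiority, and section 2.11 sizes it as such.
- **Hypothesis.** Section 1 says of PMTT that "it is equivalent in safety and efficacy to LP". The Discussion repeats the equivalence wording.
- **Margin.** Section 2.8: "The non-inferiority margin for the primary outcome is five". Section 2.12 adds "Non-inferiority margins will be set as listed in Table 2"; that table gives 5 for the JOA score and for three other outcomes.
- **Test.** Section 2.12 says that Student's t or Mann–Whitney's U "test will be used to compare continuous variables". The threshold follows: "Statistical significance will be set at" p<0.05, with no statement of one- or two-sided.
- **Estimates.** Section 2.12: "All comparative analyses will be reported with point estimates", namely means with SD or odds ratios, together with 95% CIs and p-values.
- **Population.** Section 2.12: "All data will be analyzed according to the intention-to-treat principle". No other analysis set is named.

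**The concern.** A t-test or Mann–Whitney test at p<0.05, taken as written, tests the null hypothesis of no difference. A non-inferiority trial needs to reject a different null: that PMTT is worse than LP by the margin or more. A non-significant difference test does not in itself establish non-inferiority, and a significant one does not refute it. Section 2.12 contains the parts of a correct analysis (intervals and margins) but never joins them.

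Three further gaps follow from this.

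- **Sidedness.** It is not stated, so the confidence level of the bound to be compared with the margin is open.
- **Choice of test.** Mann–Whitney remains an option for the outcome that carries the margin, and it does not itself yield a mean-difference interval in JOA points.
- **Hypothesis wording.** Equivalence requires both CI limits to lie inside the margin; non-inferiority requires only one.

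What is at stake is the primary conclusion. If the result falls where the two rules say different things, the headline could be chosen after the data are seen.

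**Working it through.** **Inputs.** SD 5.8, alpha 0.05, power 90%, 112 per group, 280 in total and 10% attrition (section 2.11); 1:1 allocation (section 2.4); JOA margin 5 (section 2.8 and Table 2). Evaluable patients per arm: 280 × 0.9 / 2 = 126.

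**The plan's own figure.** For non-inferiority with true difference 0, n = 2 × [5.8 × (1.960 + 1.282) / 5]² = 28.3, so 29 per group at one-sided 0.025. At one-sided 0.05 it is 24. The stated 112 is not reproduced; an unstated true deficit of 2.5 would come close, at 114. That is a separate matter, and nothing below depends on it.

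**Where the two rules part**
1. SE = 5.8 × √(2/126) = 0.731.
2. Half-width of the two-sided 95% CI = t(0.975, 250 df) × SE = 1.97 × 0.731 = 1.44.
3. p<0.05 against PMTT: observed deficit above 1.44.
4. Non-inferior at margin 5: observed deficit below 5 − 1.44 = 3.56.
5. Any observed deficit from about 1.44 to 3.56 points therefore satisfies both.

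**How likely that is.** In the normal approximation (half-width 1.96 × 0.731 = 1.43) with a true deficit of 2 points, the probability is Φ((2 − 1.43)/0.731) − Φ((2 − 3.57)/0.731) = 0.781 − 0.016 = 0.765. For true deficits of 1, 2.5 and 3 points it is 0.277, 0.856 and 0.765.

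**Sidedness.** If alpha 0.05 were one-sided, the bound would use t(0.95) = 1.65. The half-width becomes 1.65 × 0.731 = 1.21, and the largest deficit that passes moves from 3.56 to 3.79.

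**Does a non-significant p mislead at these inputs?** A non-significant result means an observed difference within ±1.44, so the whole 95% CI lies within ±2 × 1.44 = ±2.88, which is inside ±5. At 112 per arm the bound is ±3.05. For the CI to reach 5 at 126 per arm, the SD would have to exceed 5 / (2 × 1.97 × √(2/126)) ≈ 10.

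**Dilution under intention-to-treat (assumption).** The document gives no conversion or crossover rate. Suppose a fraction c of PMTT patients is converted and gets the full LP result, while the true deficit equals the margin. The expected intention-to-treat deficit is 5(1 − c), and the chance of a non-inferiority claim is Φ(5c/0.731 − 1.96):

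| c | Claim rate |
|---|---|
| 0% | 2.5% |
| 1% | 2.9% |
| 2% | 3.4% |
| 5% | 5.3% |
| 10% | 10.1% |
| 20% | 28% |

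**The case against.** The strongest reply is that nothing essential is missing: section 2.12 promises 95% CIs for every comparison and lists the margins, so any statistician would set one against the other. This is largely right. The defect is the absent decision rule, not absent material. It still matters, because the only decision threshold that the article states is p<0.05.

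Four stronger readings are tempting, and the document does not support them.

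- **That the two rules give opposite answers between 1.44 and 3.56 points.** They do not. Significantly worse yet non-inferior is a coherent joint result whenever the margin exceeds the CI half-width, and it would still occur under a correct rule. The fault is only that the plan does not say which result decides.
- **That a non-significant p would produce a false claim.** At SD 5.8 and 126 per arm, every non-significant result also meets the margin of 5, in both directions. The inference would be wrong in form but harmless at these inputs.
- **That an intention-to-treat population cannot support non-inferiority.** It is a legitimate primary set. Per-protocol sets break the randomised comparison, and requiring success in both is a trade-off. A supporting set may also be defined in the analysis plan, which is not shown.
- **That false claims rise to about 10%.** This rests on an assumed 10% conversion rate with full LP benefit after conversion. Under a treatment-policy reading, a diluted deficit of 4.5 really is inside the margin.

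It can also be said that a t-based interval tolerates moderate skew at this size, and that a Hodges–Lehmann shift is in JOA points. Both are fair. The plan names neither for the margin comparison, so the choice remains open.

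**Conclusion.** The point holds as a mismatch between design and stated inference. The article's tests and threshold address a null of no difference, the margins carry no decision, sidedness is unstated, and the hypothesis claims more than a one-sided margin can show. The practical size is an ambiguous zone of observed PMTT deficits from about 1.44 to 3.56 JOA points, which a true deficit of 2 points would reach about 77% of the time. This assumes an SD of 5.8 in both arms, 126 evaluable patients per arm and the margin of 5 as stated.

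The population part is secondary. Deviations and crossovers can pull the arms together, which argues for a supporting analysis. The size of that bias is unknown because the document gives no rate. A reader should not infer that the trial is likely to reach a false conclusion as planned.

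**What to change.** In section 2.12:

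1. State the primary rule: PMTT is non-inferior if the lower limit of the two-sided 95% CI for the PMTT minus LP mean JOA difference lies above minus the margin (one-sided alpha 0.025).
2. Use the p<0.05 difference test only for superiority, and only after non-inferiority is shown.
3. Base the margin comparison on a mean-difference CI, by bootstrap if the scores are skewed, and not on Mann–Whitney.
4. In section 1 and the Discussion, replace the equivalence wording with non-inferiority, or else require both CI limits to lie inside the margin.
5. Keep intention-to-treat as primary and add a supporting per-protocol analysis, with the set defined before unblinding.

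The cost is wording and one extra analysis set. The sample size and data collection do not change. If equivalence is kept as the claim, the stricter two-limit rule is also affordable: at SD 5.8, margin 5 and 90% power with no true difference it needs 35 per group at one-sided 0.025, well below the planned number.

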### Randomization and blinding

2.4.

Once written informed consent is obtained, patients would be randomized to undergo either the paravertebral approach or microtubular technique, or LP in a ratio of 1:1. The patients will be randomized using a block randomization model (block size: six). Computer-generated random number tables will be prepared by an experienced statistician. After baseline data are obtained, and a physical examination has been conducted, allocation of treatment will be performed by the computer system, and the results of the allocation will be provided to the surgeon in a concealed envelope one day before surgery. Due to the noticeable differences between the PMTT and LP procedures, blinding of the patients will not be strictly required. However, all researchers and data analysts will be blinded to the allocated intervention during the follow-up period of 2 years.

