### Baseline assessment

2.6.

The demographics, medical history, family history of tumors, results of a physical examination, body mass index, tumor location, visual analog scale (VAS) scores, and Japanese Orthopedic Association (JOA) scores will be recorded at baseline. Data will be collected prior to randomization.

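### The only stated comparison for continuous outcomes, including the primary JOA score, is an unadjusted two-group test; it is valid, but gives up precision that the recorded baseline JOA and tumor location would supply

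*Protocol article*

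**What the plan says.** Protocol article, section 2.8 (Outcome measurements): "The primary outcome variable is the JOA score". Section 2.12 (Statistical analysis) gives one rule for continuous data, Student's t or Mann–Whitney: this "test will be used to compare continuous variables". Neither that section nor any other names a covariate, a change score, a mixed model or a stratified test.

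Section 2.6 (Baseline assessment) says that "Japanese Orthopedic Association (JOA) scores will be recorded at baseline", before randomization, and its list also has "body mass index, tumor location, visual analog scale (VAS) scores". Center is not in that list, but it is known for every patient by design, since the trial has "two parallel groups in eight hospitals from seven provinces in China".

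Section 2.4 (Randomization and blinding) describes allocation "in a ratio of 1:1" by a "block randomization model (block size: six"). It states no stratification by center, tumor level or baseline JOA. Section 2.12 compares baseline data "to determine whether balanced groups were obtained after randomization", but says nothing of what follows if they are not balanced. Section 2.9 (Primary outcome) gives two JOA instruments: a cervical one with maximum 17 and another with maximum 29.

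**The concern.** The non-inferiority verdict comes from setting a confidence interval against a margin, so the width of that interval matters directly. Two recorded variables should explain part of the spread in follow-up JOA. One is the patient's own preoperative JOA. The other is tumor level, which presumably decides whether the score runs to 17 or to 29. An unadjusted comparison of pooled scores leaves both sources of variance in the estimate. Nothing in the stated allocation limits a chance difference between the groups in either variable, and the balance check has no stated consequence. If adjustment were decided only after seeing that check, the choice would be driven by the data.

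**Working it through.** **Inputs.** SD 5.8, alpha 0.05 (sidedness not stated), 90% power, 112 per group, 10% attrition, 280 in total (section 2.11); margin 5 (sections 2.8 and 2.12); 95% CIs (section 2.12). Evaluable per group: 280 × 0.9 / 2 = 126. The correlation r between baseline and follow-up JOA is not given; I assume 0.3 to 0.7.

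**The plan's own figure.** With n = 2 × SD² × (z₁₋α + z₀.₉)² / (margin − true difference)², margin 5 and true difference 0:
- one-sided 0.025: 2 × 33.64 × 10.51 / 25 = 28.3, so 29 per group;
- one-sided 0.05: 2 × 33.64 × 8.56 / 25 = 23.0, so 24 per group.

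Neither gives 112. A distance of 2.5 at one-sided 0.025 gives 114, but the article does not state that distance. This mismatch is a separate matter, and the present point does not depend on the 112.

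**Precision without adjustment.** SE = 5.8 × √(2/126) = 0.731. The 95% CI half-width is 1.96 × 0.731 = 1.43 points.

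**Precision with baseline JOA as covariate.** The variance is multiplied by 1 − r², and the equivalent n is 126 / (1 − r²).

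| Assumed r | Variance factor | 95% CI half-width | 126 per group act like |
|---|---|---|---|
| 0 | 1.00 | 1.43 | 126 |
| 0.3 | 0.91 | 1.37 | 138 |
| 0.5 | 0.75 | 1.24 | 168 |
| 0.7 | 0.51 | 1.02 | 247 |

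**Power at the stated margin.** With true difference 0, 5 / 0.731 − 1.96 = 4.88, so unadjusted power is above 99.9%. Adjustment cannot visibly improve it.

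**Power at a distance of 2.5 (illustration only).** Unadjusted: 2.5 / 0.731 − 1.96 = 1.46, or about 93%. Adjusted: about 95%, 98% and above 99% at r = 0.3, 0.5 and 0.7.

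**Chance imbalance in baseline JOA.** If the baseline SD is also 5.8 (assumption), the baseline difference between groups has a 95% range of ±1.43. About r times that passes into the follow-up difference: 0.43, 0.72 and 1.00 points at r = 0.3, 0.5 and 0.7.

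**Two scales.** Assume 30% cervical patients and a mean gap of 8 to 12 points between scales; the maxima differ by 29 − 17 = 12.
- The 95% range for a chance difference in the cervical share is 1.96 × √(2 × 0.3 × 0.7 / 126) = 0.113, or 11 percentage points. It would shift the mean difference by 0.113 × 8 = 0.9 to 0.113 × 12 = 1.4 points.
- If 5.8 is a within-scale SD, the pooled SD is √(33.64 + 0.21 × 64) = 6.86 to √(33.64 + 0.21 × 144) = 7.99. The unadjusted half-width is then 1.69 to 1.97.

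The article does not say whether 5.8 is within-scale or pooled. Baseline JOA is scored on the same scale as follow-up, so part of its correlation in pooled data would be the scale difference itself. The two gains therefore must not be added.

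**The case against.** The strongest reply is that nothing here is wrong. In a 1:1 randomized trial the two-group comparison is valid and unbiased, and its CI already allows for chance imbalance. That stands. A reader might infer that the verdict is biased or unsafe without adjustment; the documents do not support this. At margin 5 even a shift of 1.0 to 1.4 points leaves ample room when the true difference is zero.

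A second tempting reading is that the plan forgoes a rise in power from 93% to 98% or more. That rests on a distance of 2.5, which appears nowhere in the article, and on a favorable correlation that it does not give. At r = 0.3 the variance falls by only 9%.

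Third, the sentence in section 2.12 covers continuous variables in general and follows directly on the baseline comparison. It names neither a time point nor raw score versus change, and covariates are often left to an analysis plan that is not shown. This stands in part: the article does not prove that raw follow-up scores will be compared. But it is not silent on method. It names the tests, the JOA score is a continuous outcome, and neither test takes a covariate. The point is therefore an improvement on a stated method rather than a complaint about missing detail.

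**Conclusion.** The stated analysis is sound but inefficient. Adjusting for baseline JOA would narrow the 95% CI half-width from 1.43 to between 1.37 and 1.02 points, for assumed correlations of 0.3 to 0.7 with 126 per group and SD 5.8. It would also remove most of the effect of chance differences in baseline JOA and scale mix. At the stated margin of 5 with no true difference, the planned power does not change. Adjustment becomes a power gain only if the working distance to the margin is smaller than 5. That the unadjusted comparison gives up precision follows from the text; the size of the loss rests on a correlation and a scale mix that the article does not report.

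**What to change.** Prespecify, before outcome data are seen, one primary model: ANCOVA of JOA at the primary time point on treatment, baseline JOA and JOA scale or tumor level (cervical or not), with center as a further term. Name the time point when the model is written, since the article lists several visits without singling one out. Read non-inferiority from the 95% CI of the adjusted mean difference. Analyze VAS in the same way with baseline VAS. Keep the unadjusted t-test as a sensitivity analysis, and do not let the balance check decide which covariates enter.

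The cost is analysis wording only. Baseline JOA, VAS and tumor location are already recorded and center is known. The model adds 1 + 1 + 7 = 9 coefficients against about 252 evaluable patients.

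The scale term removes between-scale variance. It does not by itself justify a single 5-point margin, or a common treatment effect in points, on scales with maxima of 17 and 29; that must be settled separately.

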### Secondary outcome

2.10.

Secondary outcomes include the gross tumor resection(GTR) rate, tumor recurrence rate, VAS, assessment of back and leg pain at rest, physical examination, length of hospital stay, expenses, and complications. One of the secondary outcomes was the VAS of pain. Perceived pain intensity was measured using the VAS score [pain scale ranging from 0 (no pain) to 100 mm (the worst pain imaginable)] (14). The pain will be assessed because most patients have pain in different regions. A physical examination will be conducted at 1, 6, and 12 months after the surgery. This will include the sphincter function test, muscle strength exercise, patellar and Achilles tendon reflex assessment, and sensory assessment of the affected spinal region. Muscle strength will be scored on a scale ranging from zero (no contraction) to five (normal muscle strength) (15).

The cost-effectiveness of the hospital stay will be evaluated by summarizing the cost of the surgical procedure and the number of days before discharge. The cost of the additional procedures in case of complications will be added to the total cost of the patient's hospital stay. The primary cost of treatment will include the cost of hospital admission, surgery, medication, rehabilitation, and other healthcare utilization. The details of these charges will be registered in a diary. Immediately after the operation, a systematic assessment of complications (including cerebrospinal fluid leakage, venous thromboembolism, wound infection, urinary tract infection, hematoma, and progressive neurological deficit) will be conducted by the surgeon and research nurse until patient discharge. Surgical data will include intraoperative spinal cord and nerve root injury, operative time, and intraoperative blood loss.

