## Discussion

3.

The FJMUUH05 trial is a multicenter RCT, the first RCT of surgery for spinal IDEM tumors. To date, similar RCTs have not been reported on this topic. The trial was approved by the Chinese Clinical Trial Registry (ChiCTR, www.chictr.org.cn). The trial hypothesis is that PMTT has superior cost-effectiveness and is equivalent in safety and efficacy to LP for treating spinal IDEM tumors.

Tubular spinal surgery has gained significant prominence because of the development of minimally invasive technologies and instruments. The tubular retractor is inserted to reach the operation field by separating the paravertebral muscle and exposing the pathological lesions. This technology allows surgeons to remove tumors with two-handed operations and simultaneously use multiple microscopic instruments. Moreover, intraoperative three-dimensional imaging is another massive shift from endoscopic technology, which lets the operator conveniently operate the imaging apparatus, thereby reducing the complication rates of dural rupture. Compared with traditional surgery, fewer clinical studies have been conducted on the selection of surgical indications. The safety and effectiveness of the operation and the treatment of complications during and after the operation lack a unified opinion. The patients will be randomized to the PMTT or LP groups after tumor resection. The trial aims to study the clinical results of PMTT vs. LP for spinal IDEM tumors. This RCT study provides high-quality evidence for the efficacy of tubular spine surgery for spinal IDEM tumors. We believe that the FJMUUH05 trial will provide useful information on the long-term effects of the two treatments for spinal IDEM tumors. To date (October 2021), 11 patients have been included in the trial.

In conclusion, the FJMUUH05 trial is a multicenter RCT investigating the cost-effectiveness, safety, and effectiveness of PMTT and LP in spinal IDEM tumors. When this trial is completed with the hypothesis confirmed, it will popularize the application of PMTT and improve patient outcomes.

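### The odds ratio is the only effect measure named for categorical outcomes; a risk difference should be reported beside it for complications, gross total resection and recurrence

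*Protocol article*

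**What the plan says.** Section 2.12 (Statistical analysis) compares categorical variables by chi-square or Fisher's exact tests and sets one reporting rule for every comparative analysis: results are to be "reported with point estimates [means (SD) or odd ratios (ORs)], 95% CIs" and p-values, with significance at p < 0.05. It names no risk difference or risk ratio for between-arm comparisons. Proportions are mentioned there only for describing baseline data.

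The outcomes to which the odds ratio would apply are in section 2.10 (Secondary outcome). They are the gross total resection rate, the tumor recurrence rate, and complications comprising "cerebrospinal fluid leakage, venous thromboembolism, wound infection, urinary tract infection, hematoma, and progressive neurological deficit". No expected rate is given for any of them. Table 2 sets margins for the JOA score, VAS, muscle strength and sphincter function, but none for these binary outcomes.

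The Introduction hypothesizes that PMTT is "equivalent in safety and efficacy to LP", and the Discussion repeats this. Section 2.8 states: "The primary outcome variable is the JOA score".

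**The concern.** Equivalence in safety is a question about absolute risk: how many extra patients per 100 might be harmed by the new approach, given the data? An odds ratio needs a baseline risk before it can answer. An odds ratio of 2 is about 1 extra event per 100 patients when the control risk is 1%, and about 13 per 100 when it is 20%.

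There is also a practical difficulty. If an event is very uncommon, the sample odds ratio is zero or infinite when one arm has no events, and undefined when neither has any. The same applies to incomplete resection if nearly every tumor is fully removed. The named report for such an outcome would then be a ratio that is extreme or absent, plus a p-value above 0.05. A reader could take that p-value as support for equivalence, although the same data give a usable bound on the absolute excess.

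**Working it through.** **Inputs.** Section 2.11 gives 280 patients and 10% attrition; section 2.4 gives 1:1 allocation. So 280/2 = 140 per arm are randomized, and 140 × 0.9 = 126 per arm remain after attrition. Section 2.10 has complications assessed until discharge, and resection is a result of the operation, so 140 is the natural denominator for those. Recurrence needs follow-up, so 126 is closer for it. The article states no figure for any binary outcome, so there is nothing of its own to reproduce. All event rates and counts below are assumptions.

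**Step 1: chance that the sample odds ratio is zero, infinite or undefined.** With risk p in both arms and n per arm, P(no events in one arm) = q = (1 − p)^n. Then P(at least one arm has none) = 1 − (1 − q)², and P(both have none) = q². For n = 140 and p = 0.01: q = 0.99^140 = 0.245, 1 − 0.755² = 0.430, and q² = 0.060.

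| Assumed risk | At least one arm empty, n = 140 | Both arms empty, n = 140 | At least one arm empty, n = 126 |
|---|---|---|---|
| 0.5% | 75% | 25% | 78% |
| 1% | 43% | 6% | 48% |
| 2% | 11% | 0.3% | 15% |
| 3% | 2.8% | 0.02% | 4.3% |
| 5% | 0.15% | about 0 | 0.3% |

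The same figures apply to incomplete resection if complete resection is 99.5%, 99%, 98%, 97% or 95%. Estimability is therefore a material issue at about 2% or less and hardly any issue at 5%.

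**Step 2: what each scale reports.** For the odds ratio (OR) with event counts a and c, the Wald interval is exp(ln OR ± 1.96 × SE), with SE = √(1/a + 1/(n − a) + 1/c + 1/(n − c)). For the risk difference, Newcombe's interval combines the two Wilson limits (l, u): lower = d − √((p1 − l1)² + (u2 − p2)²), upper = d + √((u1 − p1)² + (p2 − l2)²), where d = p1 − p2.

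- 0/140 vs 0/140: the OR is undefined. The Wilson upper limit in each arm is 2.7%, so the risk difference is 0 (−2.7 to +2.7 points).
- 0/140 vs 2/140: the sample OR is 0 and has no Wald interval. The risk difference is −1.4 points (−5.1 to +1.4).
- 1/140 vs 1/140: OR 1.00 (0.06 to 16.2). The risk difference is 0 (−3.3 to +3.3 points).
- 6/126 vs 6/126 (4.8% per arm): SE = √(2/6 + 2/120) = 0.592, so OR 1.0 (0.31 to 3.19). The Wilson limits are 2.2% and 10.0%, so the risk difference is 0 (−5.8 to +5.8 points).
- 14/140 vs 14/140: OR 1.00 (0.46 to 2.18). The risk difference is 0 (−7.3 to +7.3 points).

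In the last two cases the odds ratio is perfectly estimable. Only the risk difference says directly what excess per 100 patients is excluded.

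**The case against.** The case on the other side has several parts, and most of them stand as limits on the point.

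- A reader might infer that the trial will in fact report undefined or very wide ratios because complications are rare and complete resection is nearly universal. The article does not support this: it gives no complication, resection or recurrence rate. At 5–10% the odds ratio has an ordinary interval.
- A zero in one arm does not leave the odds ratio without an interval. Section 2.12 names Fisher's exact test, and the matching exact conditional interval exists: 0/140 vs 2/140 gives 0 to 5.3, and 0/140 vs 4/140 gives 0 to 1.5. Only two empty arms leave it undefined. These intervals bound the ratio, however, and not the absolute excess.
- A reader might also infer that absolute results will be withheld. Nothing says so. Resection and recurrence are defined as rates, adverse events are to be reported, and a risk difference follows from per-arm counts. A fuller document may add measures. What stands is that the article fixes a rule for all comparative analyses, and that rule names only the odds ratio for categorical outcomes.
- The odds ratio is a valid measure, and no prespecified decision depends on the scale because these outcomes have no margin. For the same reason, a risk difference interval would not by itself establish equivalence in safety. It would show what the data exclude.

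**Conclusion.** The point holds in a limited form and is minor. The only effect measure named for categorical outcomes does not directly answer the safety half of the trial's hypothesis, and it may be inestimable for any outcome with a risk of about 2% or less. The size depends entirely on event rates that the article does not give, and the probabilities assume equal risk in both arms.

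The argument about scale does not depend on rarity, since it also applies at about 5%, where estimation is no problem. Only secondary outcomes are affected. The primary efficacy conclusion rests on the JOA score, which is not analyzed by an odds ratio. The documents do not support reading this as an error in the odds ratio or as a threat to the trial's main result.

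**What to change.** In section 2.12, add that for complications, gross total resection and recurrence the report will give per-arm counts and the risk difference (PMTT minus LP) with a Newcombe or Miettinen–Nurminen 95% CI, alongside the odds ratio. Add that statements about safety will rest on the risk difference interval and not on p > 0.05.

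This costs a sentence or two. It needs no new data or patients and leaves the primary analysis unchanged. Making the change before the data are analyzed avoids choosing the effect measure after the results are known.
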